## Abstract

Exercise‐induced hypoalgesia (EIH) has been found to vary widely within individuals with chronic neck pain (NP). Research has suggested that the presence of central sensitization within a subgroup of individuals with chronic NP might be a mediating factor to explain the relationship between exercise and improvements in patient‐reported outcomes. Furthermore, recent work has found that lactate might play a role in the development and maintenance of chronic pain. The immediate effect of a single bout of physical exercise on central sensitization in individuals with chronic NP and the relationship between lactate concentration, central sensitization and pain sensitivity are to be investigated. Eighty adult participants with chronic NP will be recruited for this randomized crossover trial. Outcome measures, including temporal summation, conditioned pain modulation, EIH and lactate concentration, will be assessed before and after low‐ and high‐intensity bicycling exercise. The outcomes of this study will provide new insights into the mechanistic effect of exercise on central sensitization in individuals with chronic NP and have the potential to add important information to the current exercise prescription guidelines for individuals with chronic NP. This study has been approved by the Human Research Ethics Committee, The University of Adelaide (H‐2022‐082) and registered in the Australian New Zealand Clinical Trials Registry (ACTRN12622000642785p).

## INTRODUCTION

1

Neck pain (NP) is one of the leading chronic musculoskeletal pain conditions, with one of the highest years‐lived‐with‐disability (YLD) and leading causes of disability (Vos et al., 2016), and YLD has increased by 29% between 1990 and 2010 (Hoy et al., 2014). The majority of the global population, ≤70%, experiences NP at least once in their lives (Safiri et al., 2020). Of this population, 50–85% may not have complete remission of symptoms and may develop chronic NP (Safiri et al., 2020).

Multiple modalities of rehabilitation, such as physical exercise, psychology, manual therapy and acupuncture, have been used as treatment for chronic NP. Among these modalities of treatment, exercise has been found to be the best evidence‐based intervention and has been an integral component of the multimodal care plan in clinical guidelines for treatment of chronic NP (Sterling et al., 2019). However, current evidence for the effectiveness of exercise interventions for improvement of pain intensity and disability of chronic NP is modest at best (de Zoete, Armfield, et al., 2020; Price et al., 2020; Sterling et al., 2019). Central sensitization (CS) has been suggested to be a mediating factor to explain the relationship between exercise and improvements in patient‐reported outcomes (Ellingson et al., 2016; Jull et al., 2007) and has been found to be present in a subgroup of chronic musculoskeletal pain populations (Kim et al., 2015; Nijs et al., 2010; Sterling et al., 2006). A recent systematic review found that exercise might alter functional characteristics of the brain in individuals with chronic musculoskeletal pain, which is associated with changes in pain processing and patient‐reported outcomes (de Zoete, Chen, et al., 2020). These findings further support previous studies that reported the influence of exercise on pain modulation (Kroll, 2015; Mannion et al., 2012). However, to date, no study has investigated the relationship between the effect of physical exercise and CS outcome measures in individuals with chronic NP.

Recent developments in neuropathology and neurophysiology have found that lactate plays a significant associative role in the development and maintenance of chronic pain (Milligan & Watkins, 2009; Wang et al., 2021). Neuroimaging studies have found that individuals with chronic pain have alterations in the structural properties of the brain and hyperactivation of the anterior cingulate cortex (ACC), both of which are believed to play a major role in the initiation, development and maintenance of chronic pain (de Zoete et al., 2022; Smallwood et al., 2013; Zhuo, 2008). In individuals with chronic pain, the hyperactivation of the ACC results in a high energy demand for lactate by the neurons as an energy source. The high lactate demand, in turn, increases the rate of astrocyte–neuron lactate transfer (ANLT) in the ACC (Suzuki et al., 2011). The increased rate of lactate transfer results in increased expression of p‐ERK, p‐CREB and Fos, which have been identified as requirements for lactate‐transfer‐mediated modulation of chronic pain (Ji & Strichartz, 2004; Ji et al., 1999). A recent study found that the disruption of the ANLT, by blocking glycogenolysis in astrocytes, can disrupt the formation of chronic pain (Wang et al., 2021). Previous studies investigating effects of exercise on chronic musculoskeletal pain reported either a hypoalgesic or hyperalgesic response depending on the modality of exercise performed, the involvement of painful or non‐painful body areas and the duration and intensity of the exercise performed (Ge et al., 2012; Lannersten & Kosek, 2010; Smith et al., 2020; Vaegter & Jones, 2020). Previous studies on aerobic exercise in chronic pain found that 30 min compared with 10 min of aerobic exercise elicited a greater dose response, with a larger effect on exercise‐induced hypoalgesia (EIH) (Hoffman et al., 2004), and there was no difference in the EIH response between 10 and 20 min of aerobic exercise (Vaegter et al., 2014). Although the underlying mechanisms of EIH are not well established, previous research has found that lactate produced in the periphery during exercise can crosses the blood–brain barrier through monocarboxylate transporters and be used as an energy source by neurons (Proia et al., 2016). We hypothesize that by increasing the availability of lactate through exercise, lactate will be transported across the blood–brain barrier via monocarboxylate transporters and taken up by the energy‐deprived neurons, fulfilling the lactate demand and disrupting glycogenolysis in the astrocytes and the ANLT. The disruption of glycogenolysis and ANLT is hypothesized to be crucial to the molecular aetiology of the persistence of pain. Therefore, this molecular bridge provides crucial new insights into the pain‐mitigating benefits of exercise.

Although the evidence indicates that exercise alters central pain modulation, it is not known whether the clinical presentation of CS is associated with the mechanistic effect of exercise on hypoalgesia. Therefore, the primary aim of this study is to investigate the immediate effect of a single bout of physical exercise on CS in individuals with chronic NP. The secondary aim is to investigate the relationship between lactate concentration ([La]), CS and pain sensitivity. With the knowledge that lactate plays an important role in the maintenance of chronic pain, we hypothesize that lactate produced during exercise will have a positive correlation with EIH. Although exercise might induce similar hypoalgesic responses across different chronic pain conditions (Polaski et al., 2019), comparing these effects across different types of chronic pain poses challenges (Rice et al., 2019). Notably, differences in the mechanisms underlying different chronic pain conditions (Bogduk, 2011; Knezevic et al., 2021; Popescu & Lee, 2020) and different management strategies and recovery trajectories have led to different clinical guidelines for different chronic pain conditions (Blanpied et al., 2017; George et al., 2021). To ensure that the findings of this trial are valid and reproducible and optimally inform clinical practice, this study focuses on chronic non‐specific NP alone in order to ensure a homogeneous population.

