**FIGURE 1 eph13343-fig-0001:**
[figure not shown]
Schedule of enrolment, interventions and assessments. Abbreviations: CPM, conditioned pain modulation; EIH, exercise‐induced hypoalgesia; GPAQ, global physical activity questionnaire; NDI, neck disability index; PCS, pain catastrophizing scale; SF‐36, 36‐item short form survey; ‐t_1_, enrolment week 0; t_0_, allocation; t_1–2_, intervention, baseline and post‐intervention assessments; TS, temporal summation; TSK, Tampa scale of kinesiophobia.

This study is a randomized crossover trial, in which all participants will take part in all interventions, but the order in which they are assigned to the interventions is randomized. Participants will attend the first data collection session, during which baseline questionnaires and physical assessments will be measured, followed by the intervention, and a post‐intervention physical assessment will be measured. There will be a 1‐ to 2‐week washout period before the second data collection session, which is identical to the first session minus the baseline questionnaires, with a different intensity of intervention.

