### Procedures

2.4

Participants who meet the inclusion criteria will be invited to attend two testing sessions: one to perform high‐intensity submaximal aerobic bicycle exercise (HIGH); and a second to complete a low‐intensity submaximal aerobic bicycle exercise (LOW). The order of these two testing sessions will be randomized. Participants will be asked to refrain from analgesics on the day of testing and to abstain from physically demanding activities, including exercise, for 48 h before testing. Participants will also be asked to abstain from nicotine, alcohol and caffeine for 12 h before testing.

Participants will be given a detailed explanation about the research study and the requirements of them. Informed consent will be obtained from the participants before collecting any data. Figure 2 depicts the flowchart of study procedure and the assessments conducted at each assessment time point. Participants will be randomized into two main groups, termed the INV‐A group and the INV‐B group, with INV‐A doing HIGH–LOW and INV‐B doing LOW–HIGH. Participants will wait 10 min before commencing the exercise intervention to prevent a carryover effect from the baseline physical assessments influencing exercise. During the waiting time, resting heart rate (HR) and blood pressure will be measured, and appropriate warnings and precautions will be briefed. Participants will then complete the assigned exercise intervention, immediately followed by postexercise assessment. The order of testing will be kept constant within each testing session, both before and after exercise. To prevent a carryover effect, the sessions will be scheduled 1–2 weeks apart.

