### Data collection

2.6

Demographics, including age, sex, education level, duration of chronic NP, physical activity participation level (GPAQ; Cleland et al., 2014) and employment status, will be collected. The outcome assessments consist of questionnaires and central pain processing measurements. Questionnaires will be assessed at the start of each exercise session, and the central pain processing measurements will be performed twice at each session: at baseline; and postexercise.

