#### LOW intervention

2.7.2

The LOW intervention will follow the same procedure as HIGH, except for the intensity of the exercise. The participant's target HR will be 50% of age‐predicted maximum HR.

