### Statistical analysis

2.9

All data will be analysed via scatterplots, boxplots and Kolmogorov–Smirnov statistics to evaluate normality. Normally distributed data will be reported as the means and 95% confidence interval. Other data will be reported as the median and interquartile range. Parametric tests will be used for normally distributed data, and non‐parametric tests for non‐normal distributed data, to analyse between‐group differences for physical outcome measures and baseline questionnaires and physical measures.

To test for carryover effects, the sum of the measured values in the sessions for each patient will be calculated and compared across the two groups with Student's unpaired *t*‐test (Wellek & Blettner, 2012). A *P*‐value of >0.05 indicates no carryover effects, and the ‘washout’ duration is sufficient. To determine the statistical difference between HIGH and LOW, the within‐subject difference in outcome parameters between both sessions will be calculated using Student's unpaired *t*‐test. If there is a statistical significance, a regression model will be conducted to evaluate the effect of exercise intensity (HIGH vs. LOW) on CS measures. The fixed effect of time (baseline and postexercise), exercise intensity and study group will be included in the model, with age as a covariate. If no statistical difference is detected, repeated‐measures ANOVA will be performed to assess significant differences between both groups; the within‐subject factor will be defined as ‘time’, with ‘group’ as a between‐subject factor. The significance level will be adjusted by the number of comparisons using Bonferroni correction.

Multivariate regression analysis will be used to analyse the association between [La] and EIH. In order to examine the relationship between individual measures of CS (EIH, CPM and TS), separate regressions will be conducted. Models will be adjusted for age, sex, education level, physical activity level, NDI, PCS and TSK. Statistical significance is set at *P* < 0.05.

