## DISCUSSION

6

There are numerous research studies and systematic reviews on the effects of exercise on chronic NP, covering a wide variety of modalities of exercise (Bertozzi et al., 2013; de Zoete et al., 2019; de Zoete, Armfield, et al., 2020; Gross et al., 2015; Price et al., 2020; Sterling et al., 2019). However, systematic reviews have found that the effectiveness of exercise interventions for improvement of pain intensity and disability of chronic NP is modest at best (de Zoete et al., 2019; Price et al., 2020; Sterling et al., 2019), with no high‐quality evidence (Gross et al., 2015). Numerous studies have suggested that the presence of CS could be a factor mediating the effectiveness of exercise (Hansen et al., 2020; Kroll, 2015; Mannion et al., 2012). The difference in the presence of CS in chronic NP patients might be one of the factors contributing to the overall modest effect of exercise. However, to date, no study has investigated the relationship between the presence of CS and the mechanistic effect of exercise on hypoalgesia. Therefore, we aim to investigate the effect of two different intensities (HIGH vs. LOW) of a single bout of submaximal aerobic exercise on measures of CS in individuals with chronic NP.

We will also conduct a new investigation into the relationship of lactate, produced during exercise, with the underlying mechanism of EIH. Recent studies have found that lactate plays a role in maintaining chronic pain through its effect on the CNS, by affecting specific neurophysiological pathways within the brain (Wang et al., 2021). Previous studies of the effect of aerobic exercise on chronic pain found that 30 min compared 10 min of aerobic exercise elicited a greater dose response, with a larger effect on EIH (Hoffman et al., 2004), and there was no difference in the EIH response between 10 and 20 min of aerobic exercise (Vaegter et al., 2014). Therefore, we hypothesize that the [La] produced during exercise could play a role in the hypoalgesic effect of exercise.

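### The primary aim (the effect of a bout of exercise on central sensitization) is broader than the design supports: the only randomised, controlled contrast is HIGH versus LOW

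*Protocol article*

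**What the plan says.** The Introduction states that "the primary aim of this study is to investigate the immediate effect of a single bout of physical exercise on CS" in people with chronic neck pain. The Abstract puts it the same way, and the Discussion adds that the study will give knowledge of the immediate effects of exercise.

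The design is a two-session crossover in which "all participants will take part in all interventions" (section 2.2). The two interventions are HIGH, with a target of 75% of age-predicted maximum heart rate (section 2.7.1), and LOW, for which "The participant's target HR will be 50% of age‐predicted maximum HR" (section 2.7.2). LOW otherwise follows the HIGH procedure. Randomisation decides only the order. No rest, sham or no-exercise session is described.

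Section 2.6 says that "the central pain processing measurements will be performed twice at each session: at baseline; and postexercise". Section 2.9 first tests HIGH against LOW. If that test is significant, a regression follows, for which "The fixed effect of time (baseline and postexercise), exercise intensity and study group will be included in the model". If it is not, a repeated-measures ANOVA follows, with time as the within-subject factor and group as the between-subject factor.

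The Discussion words the aim more narrowly: "we aim to investigate the effect of two different intensities (HIGH vs. LOW) of a single bout of submaximal aerobic exercise" on measures of central sensitization.

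**The concern.** The effect of a bout of exercise and the effect of one intensity against another are different questions, and only the second has a randomised comparator here. An answer to the first can come only from the pre-to-post change within a session. That change also contains whatever happens when time passes and the same painful battery is run a second time.

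Two wrong conclusions become possible. A significant time effect could be taken as exercise altering central sensitization when it reflects habituation, sensitization or fatigue from re-testing. A null HIGH-LOW difference could be taken as exercise having no effect when both intensities acted equally. The Discussion expects the results to influence exercise prescription, so either error would matter.

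**Working it through.** **1. Which contrast the sample size serves.** Inputs from section 2.8: means 25.0 and 42.1, SDs 19.7 and 27.2, two-sided α = 0.05, power 80%, 1:1 allocation.

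- Difference = 42.1 − 25.0 = 17.1
- Pooled SD = √((19.7² + 27.2²)/2) = 23.75
- d = 17.1/23.75 = 0.72
- A two-sample t-test needs 32 per group, 64 in all (power 80.9%)
- Allowing for 20% loss: 64/0.80 = 80

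The plan's 64 and 80 reproduce. They refer to a difference between two exercise interventions. The documents give no effect size or SD for exercise against rest, so no sample size can be worked out for that question.

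**2. What each quantity estimates.** Let E be the effect of HIGH, fE the effect of LOW, and R the shift from elapsed time and repeated testing. Assume that R is additive and the same at both intensities.

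- Pre-post change in HIGH = E + R
- Pre-post change in LOW = fE + R
- HIGH minus LOW = (1 − f)E

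The contrast removes R, which is its strength. It also removes any effect that the two intensities share.

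| f (assumed) | HIGH minus LOW |
|---|---|
| 0 | E |
| 0.5 | 0.5E |
| 1 | 0 |

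There are two equations and three unknowns (E, f, R). E cannot be recovered without knowing f or R, whatever the sample size, because R is never observed without cycling.

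The article itself cites work showing no difference in the hypoalgesic response between 10 and 20 min of aerobic exercise, alongside work showing a larger response at 30 than at 10 min (Introduction and Discussion). Those doses differ in duration, not intensity, so they do not fix f. They do show that similar responses to two doses cannot be ruled out on the article's own evidence.

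**3. What R could do to a pre-post test.** This is an illustration only; the shifts are assumed. Take 64 completers, no effect of cycling, and a one-sample t-test of the change at two-sided 0.05 (63 degrees of freedom, noncentrality = shift × √64 = 8 × shift).

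| Shift, in SDs of the change score | Noncentrality | Probability of a significant pre-post change |
|---|---|---|
| 0 | 0 | 5% |
| 0.1 | 0.8 | 12% |
| 0.2 | 1.6 | 35% |
| 0.3 | 2.4 | 66% |
| 0.5 | 4.0 | 98% |

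**4. Why R need not be zero.** Section 2.6.2 describes a battery with a wall-squat to fatigue or 3 min, triplicate algometry at two sites, a train of 10 pinprick stimuli at two sites, and an ice-bath of up to 120 s. It is run before and after cycling in the same visit.

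**5. Where section 2.9 leads after a null contrast.** The ANOVA branch has time and group. Section 2.4 defines the groups as the two sequences, INV-A (HIGH–LOW) and INV-B (LOW–HIGH). If group keeps that meaning, intensity is not a factor in this branch. The term left that bears on the aim in the Introduction is then the uncontrolled time effect.

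**The case against.** A reader might infer that the design can estimate nothing but HIGH versus LOW. The documents do not support that. Measures are taken before and after cycling in each session and time is a model term, so a within-session change can be estimated. What it lacks is a control.

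A reader might also infer that the plan intends to credit a time effect to exercise, or to read a null contrast as no effect. No passage says so. The regression is there to evaluate HIGH versus LOW and the ANOVA to compare groups. This is a risk of misattribution, not a stated rule.

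The best defence is that the Introduction gives a general aim and the rest of the article makes it operational. The sample size, the first test in section 2.9, the description of the trial under Possible risks (section 5.3) and the Discussion all concern two intensities. A light active comparator, with the same bicycle, procedure and test battery, is a legitimate dose-comparison design. The 50% target is 0.5 × (220 − 19) = 100.5 bpm at age 19 and 0.5 × (220 − 65) = 77.5 bpm at age 65. This stands, and it shows that the design is sound for the narrower question. It does not give the broader aim a comparator, and the limitations in the Discussion do not mention that one is missing.

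The protocol also guards against carryover from baseline testing. A 10 min wait, a ramp and 30 min of cycling put at least 10 + 30 = 40 min between the two batteries. That is longer than the up to 30 min for which the Discussion says exercise-induced hypoalgesia lasts. It weakens any argument from lingering hypoalgesia after the first wall-squat. It does not measure or exclude habituation, sensitization, fatigue or plain elapsed time.

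Finally, f and R have no figures in the documents, so the tables above show what could happen, not what will.

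**Conclusion.** The concern holds in this form: the primary aim in the Abstract and Introduction is broader than the design supports. HIGH versus LOW is the only randomised, controlled contrast. The pre-post change can be estimated but cannot be attributed to exercise, and a null contrast would not show that exercise does nothing.

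The contrast captures the fraction 1 − f of the HIGH effect, anywhere from all of it (f = 0) to none (f = 1). This rests on an additive re-testing effect that is equal at both intensities, with f and R unknown.

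This should be fixed, because it changes what the trial can validly conclude about its stated primary question. It is not a fatal flaw. Randomisation, sample size, data collection and the HIGH-LOW comparison are unaffected, and the Discussion already contains a workable aim.

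**What to change.** - Restate the primary aim in the Abstract and Introduction to match the Discussion: the effect of HIGH versus LOW intensity on the within-session change in EIH, TS and CPM.
- In section 2.9, name HIGH minus LOW in that change as the only randomised estimate.
- Label pre-post (time) changes, including any from the ANOVA branch, as descriptive and uncontrolled, and do not attribute them to exercise.
- State that a null HIGH-LOW result will not be read as no effect of exercise.
- Add the lack of a non-exercise comparator to the limitations in the Discussion.

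These are changes of wording. No extra session or participant is needed. The cost is a narrower claim: the trial would speak to intensity, not to whether a bout of exercise changes central sensitization.
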